# STUDY PROTOCOL

## The Effect of Spinal Orthosis on Scoliosis Progression and Chest Deformity in Children with Type 1 Spinal Muscular Atrophy: A Randomized Controlled Trial

### 1. Introduction

Spinal muscular atrophy (SMA) is an autosomal recessive neuromuscular disease caused by the deletion of the SMN1 gene located on chromosome 5, which is responsible for the production of the Survival Motor Neuron (SMN) protein. Altered production of this protein leads to degeneration of motor neurons in the anterior horn of the spinal cord, resulting in progressive denervation, muscle atrophy, and increased weakness.

After cystic fibrosis, SMA is the second most common autosomal recessive genetic disease of childhood, with a global incidence of 1/10,000 to 1/24,000 live births. The carrier frequency in the general population is approximately 1/40 to 1/60 (Di Pede et al., 2019).

SMA includes a wide range of phenotypes classified into clinical groups according to age of onset and maximum motor function achieved:

- Very weak infants who cannot sit independently (Type 1),
- Patients who can sit independently but cannot stand (Type 2),
- Ambulatory patients with childhood-onset SMA (Type 3),
- Ambulatory patients with adult-onset SMA (Type 4) (Mercuri et al., 2018).

Type 1 SMA (Werdnig-Hoffmann disease, infantile-onset) appears before 6 months of age and is the most common type of SMA (60%). These patients are severely hypotonic, with predominant proximal muscle weakness, weak cry, respiratory failure or abdominal breathing, difficulties in sucking or swallowing, tongue fasciculations, and high risk of aspiration pneumonia. They never learn to sit and, in the absence of ventilatory support, typically die from respiratory failure within the first two years of life (Mirea et al., 2022).

In these patients, intercostal muscle weakness and relative preservation of the diaphragm result in a characteristic "bell-shaped" chest and paradoxical breathing pattern (Mercuri et al., 2018). Scoliosis, defined by the Scoliosis Research Society as a three-dimensional spinal deformity with a Cobb angle of at least 10°, is most commonly observed in patients with Type 1 and Type 2 SMA (Stępień et al., 2020). Scoliosis significantly impairs pulmonary function by reducing vital capacity and increasing ventilation/perfusion mismatch (Di Pede et al., 2019). Thoracic cage distortion related to scoliosis further exacerbates respiratory disorders in SMA patients (Stępień et al., 2020). Cobb angle measured in supine position or with spinal orthosis in sitting position can be used for follow-up (Sauvagnac-Quera et al., 2016).

The advent of new treatments leading to increased survival and overall functional improvement is rapidly changing the scenario of spinal management in these patients (Finkel et al., 2018). For SMA Types 1 and 2, scoliosis >20° should be monitored every 6 months until skeletal maturity and annually thereafter. Spinal orthoses are frequently recommended to support the hypotonic trunk and manage scoliosis >20° (Fujak et al., 2011; Catteruccia et al., 2015). Since both rigid and soft thoracolumbosacral orthoses have been recommended, there is no consensus regarding the optimal brace type (Mercuri et al., 2018). No studies have been found in the literature specifically evaluating the effects of spinal orthosis in patients with Type 1 SMA. The aim of this study is to investigate the effect of spinal orthosis on scoliosis progression and chest deformity in children with Type 1 SMA.

### 2. Objectives

- **Primary Objective:** To assess the effect of spinal orthosis on scoliosis progression, as measured by the Cobb angle.
- **Secondary Objectives:**
  - To evaluate changes in bell-shaped chest deformity using the basal upper-lower chest wall ratio.
  - To assess improvements in motor function using the CHOP INTEND scale.
  - To compare the effects of spinal orthosis combined with individualized trunk exercises versus trunk exercises alone.

### 3. Methods

#### 3.1. Study Design

This study is a stratified, single-blind, parallel-group randomized controlled trial conducted at Istanbul Medipol University Hospital. Recruitment will begin on October 11, 2023, and is expected to conclude by September 10, 2024.

- **Group 1** (Pulmonary Care (PC), Individualized Pulmonary Rehabilitation (IPR), Individualized Trunk Exercise Program (ITE))
- **Group 2** (Pulmonary Care (PC), Individualized Pulmonary Rehabilitation (IPR), Individualized Trunk Exercise Program (ITE) & Spinal Orthosis)

#### 3.2 .Ethical Considerations

Ethical approval was obtained from the Non-Interventional Ethics Committee of Istanbul Medipol University (Approval No: E-10840098-772.02-200). The study is registered in ClinicalTrials.gov (NCT05878418). Written informed consent will be obtained from all participants before enrollment. All procedures adhere to the Declaration of Helsinki.

#### 3.3. Participant Selection

##### Inclusion Criteria:

- Children aged 2–6 years with a genetically confirmed diagnosis of Type 1 SMA.
- Cobb angle between 20° and 40°.
- Undergoing or completed treatment with nusinersen and onasemnogene abeparvovec (OA).

##### Exclusion Criteria:

- Acute respiratory failure or mechanical ventilation dependency.
- Previous spinal surgery.
- Additional neurological or orthopedic disorders.
- Poor adherence to spinal orthosis or exercise protocols.

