#### 3.5. Intervention Details

##### 3.5.1. Group 1:

Participants will receive an individualized trunk exercise (ITE) program along with standard pulmonary care (PC) and pulmonary rehabilitation (IPR). Exercises will be performed daily for 8 weeks, under weekly clinical supervision.

Exercises include:

- Passive and active-assisted trunk mobilization exercises.
- Core stability training through guided postural activities.
- Supine and side-lying activities to enhance trunk control.
- Gentle active resistance exercises for trunk muscles.
- Breathing exercises to enhance diaphragmatic movement.

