### **3.5.2. Group 2:**

- Participants will receive the same intervention as Group 1, with the addition of a customized thoracolumbosacral orthosis (TLSO) worn for at least 8 hours daily.

The TLSO will feature:

- An anterior window for diaphragmatic breathing.
- Lateral modifications to facilitate chest expansion.
- Soft inner padding for enhanced comfort.
- Adjustable straps to optimize spinal alignment without over-restricting movement.

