### **3.6. Outcome Measures**

Assessments will be conducted at baseline (pre-treatment) and after eight weeks of rehabilitation.

Primary Outcome Measure:

- Cobb angle will be assessed using supine spinal X-ray.

Secondary Outcome Measures:

- The basal upper-lower chest wall ratio will be evaluated using chest X-ray.
- Supine Angle of Trunk Rotation (SATRL and SATRU) will be measured using a scoliometer.
- Motor function will be assessed using the CHOP INTEND scale.
- Respiratory rate and SpO2 will be measured using pulse oximetry.
- Satisfaction with orthosis use will be evaluated using the QUEST 2.0 questionnaire.

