### **3.7. Sample Size Calculation**

A priori power analysis conducted using G\*Power 3.1 ( $f = 0.65$ ,  $\alpha = 0.05$ , power = 0.80) will indicate that a minimum of 18 participants (9 per group) will be required. Considering a potential dropout rate of 30%, 24 children will be recruited.

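### Poor adherence to the assigned treatments is written as an exclusion criterion, which can remove randomised children and gives the orthosis group an extra route out

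*Protocol*

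**What the plan says.** The exclusion criteria in Protocol section 3.3 (Participant Selection) include "Poor adherence to spinal orthosis or exercise protocols", alongside baseline facts such as earlier spinal surgery. No threshold defines poor adherence, and no period is named over which it is judged.

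Section 3.1 describes a "stratified, single-blind, parallel-group randomized controlled trial". Both groups do the exercise programme (section 3.5.1: "Exercises will be performed daily for 8 weeks, under weekly clinical supervision"). Only Group 2 has the brace: section 3.5.2 gives it the Group 1 programme "with the addition of a customized thoracolumbosacral orthosis (TLSO) worn for at least 8 hours daily".

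On timing, section 3.6 says "Assessments will be conducted at baseline (pre-treatment) and after eight weeks of rehabilitation". No run-in, trial fitting or earlier brace use is required anywhere. Section 3.7 states that "a minimum of 18 participants (9 per group) will be required" and then: "Considering a potential dropout rate of 30%, 24 children will be recruited".

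**The concern.** An exclusion criterion should be decidable before allocation and should mean the same thing in both groups. This one appears to be neither. Adherence to a brace supplied by the trial, or to an eight-week trial exercise programme, is observed only once treatment is under way, and a Group 1 child has no trial brace to adhere to.

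If the rule is applied during the trial, the children who remain are no longer the groups that randomisation formed, and Group 2 is filtered on one ground more than Group 1. Children who cannot keep to a brace may well differ in prognosis, so the filter can create a difference in Cobb angle that the orthosis did not cause. Because poor adherence is undefined, removal would be a matter of judgement. The blinding that section 3.4 describes covers the assessors and the statistician who randomises, not the staff or families who would see non-adherence.

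**Working it through.** **Step 1: can the rule be decided at screening?** Adherence to the orthosis needs an orthosis. Section 3.5.2 supplies it after allocation, to Group 2 only. Adherence to the exercises needs the programme in section 3.5.1, which is also trial treatment. With no run-in and no required earlier use, the natural reading is that the rule concerns behaviour after randomisation. The grounds for exclusion are then:

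| Ground | Group 1 | Group 2 |
|---|---|---|
| Poor adherence to exercises | possible | possible |
| Poor adherence to orthosis | not applicable | possible |

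**Step 2: group size.** Section 3.7 gives 18 children and a 30% allowance: 18 × 1.3 = 23.4, rounded up to 24, or 12 per group at equal allocation. With f = 0.65, so d = 2 × 0.65 = 1.30, the minimum of 18 is reproduced by a one-sided t-test (power 0.796 at 8 per group, 0.840 at 9). Section 3.7 does not state sidedness. The present point needs only the 12 per group.

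**Step 3: size of a spurious effect.** The protocol gives neither the number removed nor the link between adherence and outcome, so both are assumed. Let there be no true effect, let the outcome be standard normal with higher values better, and let it have correlation ρ with adherence. Removing the k least adherent of 12 raises the group's expected mean by ρ × m(k), where m(k) is minus the sum of the k lowest expected normal order statistics, divided by 12 − k. The three lowest of 12 are about −1.630, −1.116 and −0.793, so:

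- m(1) = 1.630 / 11 = 0.148
- m(2) = 2.746 / 10 = 0.275
- m(3) = 3.539 / 9 = 0.393

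With 3 removed from Group 2, the spurious benefit is ρ × (m(3) − m(k₁)), where k₁ is the number removed from Group 1 for exercise. For k₁ = 0 and ρ = 0.7 this is 0.7 × 0.393 = 0.28 SD. Type I error is from simulation (40,000 runs per setting, pooled two-sided t-test at 0.05), rounded to whole per cent.

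| Removed from Group 1 | Spurious benefit, ρ = 0.3 / 0.5 / 0.7 | Two-sided type I error |
|---|---|---|
| 0 | 0.12 / 0.20 / 0.28 SD | 6% / 7% / 10% |
| 1 | 0.07 / 0.12 / 0.17 SD | 5% / 6% / 8% |
| 2 | 0.04 / 0.06 / 0.08 SD | 5% / 6% / 7% |

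In the first row the excess is nearly all in one direction: significant results favouring the orthosis occur in 4.5%, 6.3% and 9.3% of runs, against a nominal 2.5%. At ρ = 0 there is no bias in any row.

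**Step 4: power.** For a two-sided t-test at d = 1.30, the noncentrality is d × √(n₁n₂ / (n₁ + n₂)).

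- 12 v 12: 1.30 × √(144/24) = 3.18 on 22 degrees of freedom, power 0.861.
- 12 v 9: 1.30 × √(108/21) = 2.95 on 19 degrees of freedom, power 0.799.
- 11 v 9: power 0.781.
- 10 v 9: power 0.760.

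**The case against.** Four points count against a stronger version of this.

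- **Prior adherence.** The line stands among screening criteria, and the Introduction says that orthoses are often recommended above 20°, while every eligible child has a Cobb angle of 20° to 40°. Some candidates could therefore have a history of brace use, and the rule might mean known poor adherence before enrolment. That reading is possible. The text, however, mentions no past use and the inclusion criteria require none; if this is the intent, the wording must say so.
- **Losses in one group only.** A reader might infer that only Group 2 can lose children. The documents do not support that, since the criterion also names the exercises, which both groups do. What stands is that Group 2 has one route more. Exercise removals in Group 1 offset part of the bias, as the lower rows of the table show.
- **Bias as a certainty.** A reader might infer that the trial is biased towards the orthosis. That needs two further steps: excluded children must drop out of follow-up or analysis, and adherence must be related to outcome. The protocol states neither. The allowance for dropout suggests that some children will be lost, but it is not a rule about exclusions. That poor adherers would do worse is plausible; no passage says so.
- **No stated analysis set.** A reader might count this as a separate error. It is not one, because analysis sets are commonly left to the statistical analysis plan, which is not shown. An all-randomised analysis defined there would reduce the harm, but it would sit awkwardly with section 3.3, and it could not recover a week-8 radiograph that was never taken.

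**Conclusion.** The point holds in conditional form. As worded, section 3.3 turns adherence to the assigned treatments into an eligibility rule, and its orthosis part can apply only to Group 2. That follows from the protocol alone.

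Bias is a consequence only if excluded children leave follow-up or analysis and adherence is related to outcome; its probable direction is towards the orthosis. Its size cannot be derived from the protocol. The range of about 0.04 to 0.28 SD, with type I error of about 5% to 10%, rests on assumed removals (3 of 12 in Group 2, 0 to 2 of 12 in Group 1) and assumed correlations (0.3 to 0.7). With no correlation, the cost is power alone. The rule should be changed before the primary Cobb angle comparison relies on it, because the correction is cheap and the sample is small.

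**What to change.** Delete the line from section 3.3, or limit it to facts known before randomisation and applied in the same way to both groups, for example that the caregiver is willing to accept either allocation.

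State that a week-8 radiograph is sought for every randomised child regardless of adherence, and that children are analysed in the group to which they were allocated. Report brace wear time and exercise adherence by group, and label any adherent-only analysis as a sensitivity analysis.

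The change is one of wording and needs no extra recruitment. It does require week-8 assessment of children who are not following the programme. The downside is that the effect estimate then includes non-wearers and may be somewhat smaller.

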#### 3.4. Randomization & Blinding

Stratified randomization based on Cobb angle and age will be performed using Research Randomizer. Six strata will be created. A statistician blinded to group allocation will conduct the randomization. Assessors will be blinded.

#### 3.5. Intervention Details

##### 3.5.1. Group 1:

Participants will receive an individualized trunk exercise (ITE) program along with standard pulmonary care (PC) and pulmonary rehabilitation (IPR). Exercises will be performed daily for 8 weeks, under weekly clinical supervision.

Exercises include:

- Passive and active-assisted trunk mobilization exercises.
- Core stability training through guided postural activities.
- Supine and side-lying activities to enhance trunk control.
- Gentle active resistance exercises for trunk muscles.
- Breathing exercises to enhance diaphragmatic movement.

### **3.5.2. Group 2:**

- Participants will receive the same intervention as Group 1, with the addition of a customized thoracolumbosacral orthosis (TLSO) worn for at least 8 hours daily.

The TLSO will feature:

- An anterior window for diaphragmatic breathing.
- Lateral modifications to facilitate chest expansion.
- Soft inner padding for enhanced comfort.
- Adjustable straps to optimize spinal alignment without over-restricting movement.

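### The protocol prescribes daily orthosis wear and excludes for poor adherence, but names no way of recording wear or exercise sessions

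*Protocol*

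**What the plan says.** Section 3.5.2 gives Group 2 everything that Group 1 receives, plus a customised orthosis "worn for at least 8 hours daily". The orthosis is therefore the whole contrast between the arms.

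On the shared exercise programme, section 3.5.1 says: "Exercises will be performed daily for 8 weeks, under weekly clinical supervision".

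Section 3.6 sets two assessment times: "Assessments will be conducted at baseline (pre-treatment) and after eight weeks of rehabilitation". The primary outcome is stated as "Cobb angle will be assessed using supine spinal X-ray". The secondary outcomes are the chest wall ratio, trunk rotation, CHOP INTEND, respiratory rate with SpO2, and one item about the device: "Satisfaction with orthosis use will be evaluated using the QUEST 2.0 questionnaire".

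Adherence appears once in the protocol, among the exclusion criteria of section 3.3: "Poor adherence to spinal orthosis or exercise protocols". No measure, threshold or time point goes with it. No diary, sensor, log or other record of wear or of exercise sessions is named anywhere.

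**The concern.** The protocol prescribes a daily amount of wear and relies on adherence as a criterion, but gives no means of knowing what was worn or done. Two things are at stake.

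- **Reading the result.** If the arms do not differ on Cobb angle, the reader cannot tell an orthosis that was worn and did not help from one that was worn little. If they do differ, the result cannot be tied to an amount of wear.
- **The adherence exclusion.** Adherence to the trial orthosis can be seen only after allocation and only in Group 2. Applied during the trial, the criterion could remove children from one arm on a judgement that no listed data support. That would weaken the balance that randomisation provides.

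This is not a matter for the SAP. An SAP can analyse only what was collected, and daily wear that goes unrecorded during the eight weeks cannot be recovered later.

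**Working it through.** **Setting the sections side by side**

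| Item | Where | Does it record wear or sessions? |
|---|---|---|
| Orthosis prescription | 3.5.2 | No; it states what is prescribed |
| Daily exercise, weekly supervision | 3.5.1 (shared with Group 2 through 3.5.2) | A contact exists; nothing is said to be recorded there |
| Cobb angle, chest ratio, trunk rotation, CHOP INTEND, respiratory rate, SpO2 | 3.6 | No |
| QUEST 2.0 | 3.6 | No; it is listed as a measure of satisfaction |
| Poor adherence as exclusion | 3.3 | No; it needs such a record but names none |

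**The plan's own sample size**

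Inputs from section 3.7: f = 0.65, alpha = 0.05 (sidedness not stated), power = 0.80, from which "a minimum of 18 participants (9 per group) will be required", with 24 recruited to allow for 30% dropout. For two equal groups d = 2f = 2 × 0.65 = 1.30.

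- Repeated-measures ANOVA, between-groups factor, two measurements, assumed correlation 0.5: noncentrality = f² × N × 2 / (1 + 0.5) = 0.4225 × 18 × 2 / 1.5 = 10.14, power 0.848. The smallest N is 18, so this reproduces the plan.
- One-sided two-sample t-test, d = 1.30: 9 per group, power 0.840. This also reproduces the plan.
- Two-sided two-sample t-test, d = 1.30: power 0.735 at 9 per group; 11 per group are needed for 0.80.
- Dropout: 18 × 1.3 = 23.4, rounded up to 24, as stated.

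**Illustration: what low wear could do**

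The documents give no actual wear and no dose-response. Assume that the effect is proportional to the fraction w of prescribed wear achieved, and that d = 1.30 applies at w = 1. Then d(w) = 1.30 × w. The test is the independent-samples t-test of section 3.8, taken as two-sided at 0.05, with noncentrality d(w) × √(n/2) and 2n − 2 degrees of freedom.

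- n = 9, w = 1: 1.30 × √4.5 = 2.758, critical value 2.120, power 0.735.
- n = 9, w = 0.5: 0.65 × √4.5 = 1.379, power 0.254.
- n = 12, w = 1: 1.30 × √6 = 3.184, critical value 2.074, power 0.861.
- n = 12, w = 0.5: 0.65 × √6 = 1.592, power 0.331.

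| Wear fraction | d | Power, 9 per group | Power, 12 per group |
|---|---|---|---|
| 1.00 | 1.30 | 0.735 | 0.861 |
| 0.75 | 0.975 | 0.494 | 0.627 |
| 0.50 | 0.65 | 0.254 | 0.331 |
| 0.25 | 0.325 | 0.099 | 0.119 |

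Under the two variants that reproduce N = 18, half wear takes power from 0.848 to 0.322 (repeated measures) and from 0.840 to 0.373 (one-sided). The direction does not depend on the choice of test.

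The table measures low wear, not the failure to record it. A log would leave every figure unchanged.

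**The case against.** A reader might infer that the trial collects nothing on adherence. The protocol does not say so. Section 3.6 lists outcome measures; adherence is a process variable, and the list is not declared to cover all data recorded. The supportable statement is that no method is named. Nor does the protocol say where the orthosis is worn, so unsupervised home use is an inference. Group 2 shares the weekly supervised contact, where wear could be asked about, although the text does not say that it is.

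A reader might also infer that without wear data the trial cannot describe the treatment it tested, or that its comparison is invalid. Neither follows. Section 3.5.2 describes the assigned treatment, and the randomised groups still estimate the effect of assigning it. Only the explanation of the result suffers.

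The power figures are open to four fair objections, and all stand:

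- Proportionality to wear is assumed.
- Section 3.7 does not say what level of wear f = 0.65 reflects. If it already allows for imperfect wear, scaling it down counts the loss twice.
- The prescription is a minimum, and wear above it is ignored.
- At 9 per group the two-sided t-test gives 0.735 even at full wear, so a null could be inconclusive with perfect adherence.

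What the objection does not remove is the conflict between sections 3.3 and 3.6: an adherence criterion is stated, and no measure for it is named.

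**Conclusion.** The point holds as a gap in data collection that should be closed. It does not invalidate the comparison. The protocol prescribes daily wear, makes poor adherence an exclusion, and names no record of wear or exercise. As written, a null result could not be separated from low wear, and an adherence exclusion would be undocumented and, for the orthosis, confined to Group 2.

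The gap itself has no numerical size. By way of illustration, under an effect proportional to wear, d = 1.30 at full wear and a two-sided t-test, an orthosis that works as planned but is worn half the prescribed time would miss significance with probability 1 − 0.254 = 0.746 at 9 per group and 1 − 0.331 = 0.669 at 12. Low wear alone could thus plausibly produce a null. These figures do not measure the harm of failing to record wear.

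No view is taken on whether the prescribed hours are right.

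**What to change.** - **Section 3.6:** add a one-line daily caregiver log of orthosis hours (Group 2) and exercise sessions done (both groups). It is collected at the weekly supervision that section 3.5.1 already provides, by someone other than the blinded assessors, because a wear log reveals the arm.
- **Reporting:** give mean hours per day and the percentage of days reaching the prescribed hours beside the primary result, together with sessions done in each arm. Use these for description only.
- **Section 3.3:** state that adherence after randomisation does not remove a child from the primary comparison.

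The cost is one short form and a small burden on caregivers, with no extra visit. The protocol does not say whether the weekly supervisors also act as blinded assessors; if they do, another person must collect the form. Self-reported hours tend to be overstated, so the log will only partly settle a null result.
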